### Outcome measures and participant timeline

#### Outcome measures

Baseline dataDemographic data will be recorded using a general information questionnaire, which we designed in house. The questionnaire includes questions on age, gender, education, occupation, weight, and height.Clinical characteristics will be recorded using another in-house-designed questionnaire. Specifically, data will be collected on the surgery time, anesthesia time, intraoperative blood loss, intraoperative fluid transfusion volume, and vital signs (temperature, heart rate, respiratory rate, and blood pressure).Primary outcome measureThe primary outcome is the time to first passage of flatus—we will begin observing and recording when subjects return safely to the ward, and the subjects and their families will be asked to record the time of the first passage of flatus. The interval between the two time points will be then calculated.Secondary outcome measuresTime to first defecation: We will observe and record when the subjects return safely to the ward, and the subjects and their families will be asked to record the time of first defecation. The interval between the two time points will then be calculated.Abdominal pain: The subjects’ degree of postoperative pain will be assessed using the VAS scale [10]. The first evaluation will be performed 6 h after surgery, immediately before the first treatment. Evaluations will then be carried out once every 12 h, for seven evaluations. Assistance will be given to subjects and their families in recording this information.Abdominal distention: The Likert scale will be used to assess the subjects’ degree of postoperative abdominal distention [11]. The first evaluation will be performed 6 h after the surgery, immediately before the first treatment. Evaluations will then be carried out once every 12 h, for seven evaluations. Assistance will be given to subjects and their families in recording this data.Nausea: The VAS scale will be used to assess subjects’ degree of postoperative nausea [10]. The first evaluation will be performed 6 h after the surgery, immediately before the first treatment. Evaluations will then be carried out once every 12 h, for seven evaluations. Assistance will be given to subjects and their families in recording this data.Vomiting: The frequency of postoperative vomiting will be recorded. The first evaluation will be performed 6 h after the surgery, immediately before the first treatment. Evaluations will then be carried out once every 12 h, for seven evaluations. Assistance will be given to subjects and their families in recording this data.Mental status: The Hospital Anxiety and Depression Scale (HADS) will be used to assess the subjects’ postoperative mental status [12]. The HADS consists of 14 items: seven assess depression, and the other seven assess anxiety. The scores of the anxiety and depression subscales are classified as follows: 0–7 points indicate no symptoms, 8–10 points indicate suspected symptoms, and 11–21 points indicate confirmed symptoms. The first evaluation will be performed 24 h before surgery, and the second evaluation will be performed on the day of discharge.Quality of life: the Gastrointestinal Quality of Life Index (GIQLI) will be used in this study [13]. The GIQLI aims to measure the quality of life of subjects with digestive diseases and includes five domains: subjective symptoms, physiological functional status, daily life, social activities, and psychological and emotional state. Within these domains, 36 items are assessed, each with a score from 0 to 4 points, for a total possible score of 144 points. The normal population will score 12–125 points. The first evaluation will be performed 24 h before surgery, and the second will be conducted 2 weeks after discharge. A follow-up evaluation will be carried out 1 month after discharge. Higher scores indicate better health status.Safety indicatorsAn event can be defined as an adverse event if at least four subjects suffer a symptom—such as local skin allergies, dizziness, and low blood sugar—during the treatment-evaluation period. These events will be statistically analyzed, and treatment safety is evaluated on this basis, in accordance with the research protocol. If serious adverse events occur, they will be immediately reported and managed accordingly.Participant timelineFor a complete overview of the time schedule of enrollment, interventions, and assessment for participants, see Fig. 4.

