### Sample size estimation and statistical analysis

#### Sample size estimation

This study consists of two groups; the sample size-estimation formula is therefore based on a two-group, parallel, controlled design:$$ n=\frac{{\left({\mathrm{Z}}_{1-a/2}+{\mathrm{Z}}_{1-\beta}\right)}^2\times \left({\sigma}_1^2+{\sigma}_2^2\right)}{\delta^2}, $$where *n* represents the sample size in each group, σ represents the standard deviation, and *δ* represents the between-group difference with clinical significance. At an α value of 0.05, a power of 80 %, and given a two-sided test, we obtained Z scores of Z_1 − *a*/2_ = 1.96 and Z_1 − *β*_ = 0.84 from the Z score table. Eight subjects recruited from November 2015 to December 2015 were included in the pilot trial, and the primary outcome measure was the time to first flatus: *S*_1_ = 3.14 and *S*_2_ = 5.58. A decrease of 4 h in the time to first flatus was set as our clinical expectation based on preliminary tests and clinical experience. The above data were used to estimate the value of the overall parameter to be inserted into the above formula, and an n-value of 20.09 was obtained. Therefore, the rounded sample size in each group was 21; assuming a 15 % dropout rate, the final sample sizes in the experimental and control groups would be 25 cases, yielding the required 50 cases.

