#### Statistical analysis

Content of statistical analysisSample distribution: The absolute number of dropouts as well as the rate will be described for each data set. These data will be analyzed, and the reasons for each termination are listed in detail.Balance comparison: The subjects’ general information will be compared to assess the comparability of the two groups.Efficacy analysis: The subjects’ time to first passage of flatus will be used as the primary outcome measure to evaluate the efficacy and safety of APP in treating gastrointestinal dysfunction after laparoscopic cholecystectomy. The means and standard deviations will be calculated to describe the outcome measure, and the experimental and control groups will be statistically compared using two independent-sample *t* tests. The subjects’ time to first defecation, abdominal pain, abdominal distention, nausea, vomiting, mental status, and quality of life—i.e., the seven secondary outcome measures—will be used to evaluate the efficacy of the APP. Six of these—namely, the time to first defecation, abdominal pain, abdominal distention, nausea, vomiting, and quality of life—will be described using mean ± standard deviation. The scores for mental status will be recorded and categorized in terms of the classification criteria. The statistical analysis of time to first defecation is the same as that of time to first passage of flatus; abdominal pain, abdominal distention, nausea, vomiting, and quality of life will be statistically compared between groups using Repeated Measures Analysis of Variance (RMANOVA). However, before the RMANOVA is performed, a sphericity test will be used to determine whether the data are suitable for analysis using RMANOVA. If the data do not meet the conditions of sphericity, the correction factor *ε* will be used to correct the degree of freedom before the RMANOVA is performed. The categorical measure of mental status will be analyzed using either the rank-sum test or Spearman’s rank correlation.Safety analysis: In accordance with the above definitions of adverse events, we compiled a list describing, grading, and explaining the adverse events in detail. We will ascertain descriptive statistics of the absolute number—as well as the incidence—of each adverse event in both groups. When making comparisons, we will use the *χ*^2^ test or Fisher’s exact test for statistical analysis.Methods of statistical analysisData will be analyzed in accordance with the principle of intention-to-treat (ITT). That is, we will include all subjects who were treated at least once in the trial. Efficacy and safety measures will be analyzed in accordance with “per-protocol” (PP), whereby we will include all subjects who completed the entire trial and followed the protocol requirements. Quantitative variables in the trial data will be expressed as $$ \overline{\mathrm{X}}\pm \mathrm{S}\mathrm{D} $$ for statistical description, whereas qualitative variables will be recorded as the number of cases in each category. If the quantitative variables constitute repeated measures data, then RMANOVA will be used for comparison, and the sphericity test will be used to determine the suitability of, as well as to correct, the data. Qualitative variables will be analyzed using either the rank-sum test or Spearman’s rank correlation; count data for incidence will be compared using the *χ*^2^ test or Fisher’s exact test. All statistical tests are two-sided, and differences with *P* values < 0.05 will be considered statistically significant. Statistical analysis will be performed using SPSS 19.0 statistical software for calculations.

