
## Discussion

Anesthesia, carbon dioxide pneumoperitoneum, surgical trauma, inflammation, postoperative bed rest, and other factors can cause postoperative gastrointestinal dysfunction in LC patients. Such adverse effects can lead to prolonged hospitalization, prevent patients from recovering functionally, and increase the medical burden.

Currently, postoperative gastrointestinal dysfunction is treated using postoperative fasting, gastrointestinal decompression, early ambulation, enema, chewing gum, gastroprokinetic drugs, and early enteral nutrition [14–16]. In this regard, APP using vaccaria seeds has clear benefits for patients with diseases of the digestive system [17, 18]. This study is the first standardized, scientific, clinical trial to evaluate the efficacy and safety of APP treatment using vaccaria seeds for postoperative gastrointestinal dysfunction. The study was prompted by long-term clinical experience and will use the time to first passage of flatus as the primary outcome measure. We wish to provide a scientific basis upon which to promote this therapy.

A systematic review [1] showed that the time to first passage of flatus has important clinical significance in terms of recovering gastrointestinal motility, and the same parameter is closely related to the recovery of the postoperative gastrointestinal dysfunction. For this reason, most clinical trials addressing the treatment of postoperative gastrointestinal dysfunction, such as that by Cho in 2015 [19] and that by Kim in the same year [20], use the time to first passage of flatus as a primary outcome. In this way, they can evaluate the recovery of gastrointestinal function. Hence, we also have set this measure as the primary outcome in our trial. During the perioperative period, subjects may exhibit psychological changes such as anxiety and depression [21]; thus, the subjects’ anxiety and depression will be used as secondary indicators of recovery. Furthermore, subjects’ quality of life within a month of discharge can also indicate the longer-term effects of this therapy.

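### If the repeated-measures group effect runs over all evaluations, the pre-treatment score dilutes it; for flatus time, one recorded covariate is a cheap optional gain

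*Protocol article*

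**What the plan says.** Outcome measures schedules pain, distention and nausea at seven evaluations. The first is at 6 h after surgery, immediately before the first session, and the rest follow at 12 h intervals. GIQLI is scored three times: 24 h before surgery, 2 weeks after discharge and 1 month after discharge. Statistical analysis compares all of these between groups by repeated-measures ANOVA, with a sphericity test and an epsilon correction. It does not say which model term carries the comparison, and it does not treat the pre-treatment value differently from the later ones. (Vomiting goes into the same analysis. It is a count and is left aside here.)

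For flatus time, "the experimental and control groups will be statistically compared using two independent-sample" t tests, with no covariate. Under the baseline data, "data will be collected on the surgery time, anesthesia time, intraoperative blood loss, intraoperative fluid transfusion volume", on a questionnaire separate from the demographic one. The only stated baseline analysis is that the subjects' "general information will be compared to assess the comparability of the two groups". General information is the name given to the demographic questionnaire, so the operative data have no stated analytic use. The Discussion observes: "Anesthesia, carbon dioxide pneumoperitoneum, surgical trauma, inflammation, postoperative bed rest, and other factors can cause postoperative gastrointestinal dysfunction".

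**The concern.** A score taken before the first session cannot carry a treatment effect. Averaged into the group comparison as if it were an outcome, it pulls the estimated difference towards zero. It is also then not used for what it does well, which is to explain why subjects differ later. The loss is largest for GIQLI, where one evaluation in three precedes treatment. In a trial of 50 subjects, a real effect on a secondary outcome could be missed for this reason alone.

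The same thought applies more weakly to the primary outcome. Anesthesia time is recorded and is fixed before the first session, so acupressure cannot change it. The flatus clock starts on return to the ward, so operating time is not part of the outcome. If anesthesia time predicts flatus time, the unadjusted test leaves explainable variance in the error term.

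**Working it through.** **Repeated outcomes.** Inputs from Outcome measures: m = 7 evaluations (p = 6 after treatment begins), or m = 3 for GIQLI (p = 2). Assumptions: equal variances (set to 1), a common correlation ρ between any two evaluations (compound symmetry), and a constant effect τ at every post-treatment evaluation. The documents give no ρ, so 0.3, 0.5 and 0.7 are shown.

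1. Group effect averaged over all m evaluations. The expected difference is (p/m)τ, that is 6/7 (a 14% loss) or 2/3 (a 33% loss). The variance of a subject's mean is (1 + pρ)/m. Information per subject: I₁ = (p/m)² / [(1 + pρ)/m] = p² / [m(1 + pρ)].
2. Post-treatment mean with the pre-treatment value as covariate. The full τ is kept. Residual variance is v − ρ², where v = [1 + (p − 1)ρ]/p. Information: I₂ = 1/(v − ρ²).
3. Relative efficiency is I₂/I₁.

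| | ρ | I₁ | v − ρ² | I₂ | I₂/I₁ |
|---|---|---|---|---|---|
| Seven evaluations | 0.3 | 36/19.6 = 1.84 | 0.417 − 0.09 = 0.327 | 3.06 | 1.7 |
| | 0.5 | 36/28 = 1.29 | 0.583 − 0.25 = 0.333 | 3.00 | 2.3 |
| | 0.7 | 36/36.4 = 0.99 | 0.75 − 0.49 = 0.26 | 3.85 | 3.9 |
| GIQLI | 0.3 | 4/4.8 = 0.83 | 0.65 − 0.09 = 0.56 | 1.79 | 2.1 |
| | 0.5 | 4/6 = 0.67 | 0.75 − 0.25 = 0.50 | 2.00 | 3.0 |
| | 0.7 | 4/7.2 = 0.56 | 0.85 − 0.49 = 0.36 | 2.78 | 5.0 |

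A ratio of 2.3 means that the all-evaluations test would need about 2.3 times the subjects for the same precision relative to the effect.

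**Primary outcome.** Inputs from Sample size estimation: two-sided α 0.05, power 80%, SDs 3.14 and 5.58, difference 4 h.

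1. The plan's own figure: (1.96 + 0.84)² × (3.14² + 5.58²)/4² = 20.09, rounded to 21 per arm; 21/0.85 = 24.7, so 25 per arm and 50 in total. All reproduce.
2. Root-mean-square SD: √[(3.14² + 5.58²)/2] = 4.53 h. Unadjusted power from the noncentral t: 79.8% at 21 per arm (standard error 4.53 × √(2/21) = 1.40, df 40) and 86.4% at 25 per arm.
3. With one covariate: df = 2n − 3 = 39; expected variance inflation from chance covariate imbalance 1 + 1/(2n − 4) = 1 + 1/38 = 1.026; residual SD = 4.53 × √(1 − R²). R², the share of within-arm variance explained, is assumed.

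| R² | Power, 21 per arm | Power, 25 per arm |
|---|---|---|
| unadjusted | 79.8% | 86.4% |
| 0 | 78.7% | 85.7% |
| 0.05 | 80.7% | 87.4% |
| 0.10 | 82.8% | 89.1% |
| 0.20 | 86.9% | 92.3% |
| 0.30 | 90.9% | 95.1% |

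The break-even R² is about 0.027 at 21 per arm and 0.022 at 25. With two covariates it is about 0.054 and 0.044, and power at R² = 0 and 21 per arm falls to 77.6%.

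**The case against.** On the repeated outcomes, the protocol may intend the group-by-time interaction, and the dilution to 6/7 or 2/3 would then not apply. This is fair, because the text does not settle it. But under the same assumptions a constant effect shows in the interaction only as a change from the pre-treatment value, with variance v + 1 − 2ρ. With seven evaluations that is 0.817, 0.583 or 0.35 at ρ = 0.3, 0.5 or 0.7, so using the covariate is still 2.5, 1.75 or 1.35 times as efficient. For GIQLI it is 1.05, 0.75 or 0.45, and the ratio is 1.9, 1.5 or 1.25. The interaction test also spreads this one contrast over six degrees of freedom (two for GIQLI). The case for the covariate survives, with different ratios.

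On flatus time, the case against is strong and most of it stands. A reader might infer that the unadjusted t test is biased, underpowered or exposed to chance imbalance. The documents do not support that: under randomization its error rate already allows for chance imbalance, the trial is sized for exactly this test, and the planned power is reached. A reader might also infer that the protocol names surgery and anesthesia time as causes. The Discussion names anesthesia and surgical trauma, says nothing of their duration and gives no strength of association; the step to duration is an inference. Nor is adjustment free. The population is narrow (ASA I–II, age 18–65, cholecystectomy alone, no earlier abdominal surgery, body weight not above 80 kg), so a low R² is plausible.

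The choice of standard error matters too. In simulations of a two-covariate model at 21 per arm with the protocol's unequal SDs, HC3 errors gave power of about 78%, 82% and 87% at R² of 0.10, 0.20 and 0.30, while HC0 errors with a normal reference gave a type I error of about 7%. Finally, the time of randomization is not stated, and allocation might precede surgery. Anesthesia time is then safe as a covariate only if those running the operation do not know the allocation.

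**Conclusion.** The point on the repeated outcomes is the stronger of the two. It is conditional on the group effect being tested over all evaluations, which the text allows but does not state. The dilution to 6/7 or 2/3 assumes only a constant post-treatment effect. The ratios of 1.7 to 3.9 (2.1 to 5.0 for GIQLI) also rest on compound symmetry and on an assumed ρ of 0.3 to 0.7.

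The point on flatus time is an option, not a defect. With anesthesia time as the one covariate, power at 21 per arm changes by about −1 point at R² = 0 and +11 points at R² = 0.30. The table assumes a common residual SD; a robust standard error would take back part of the gain.

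**What to change.** For pain, distention, nausea and GIQLI, model only the post-treatment evaluations (six, or two for GIQLI), enter the pre-treatment value as a covariate, and name the group contrast that will be reported. This replaces an unspecified term with a stated one and costs one degree of freedom per model.

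For flatus time, consider prespecifying a linear model on group and anesthesia time, with a standard error that is valid in small samples and is named in advance. Keep the two-sample t test as a sensitivity analysis. One covariate is enough: surgery time probably overlaps heavily with anesthesia time (an assumption), and a second covariate doubles the break-even R². The cost is one degree of freedom and about 1 point of power if the covariate is not prognostic. State when randomization takes place relative to surgery.

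No new data are needed. Trial status reports that recruitment is ongoing, so both changes can be fixed before unblinding.

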**Methods/design:**

This study is a randomized, double-blind, controlled, single-center, clinical, pilot trial. It has been designed according to the Consolidated Standards of Reporting Trials (CONSORT 2010) guidelines as well as the Standards for Reporting Interventions in Controlled Trials of Acupuncture (STRICTA). Study subjects are being selected from among hospitalized patients who have undergone laparoscopic cholecystectomy at the Department of Minimally Invasive Surgery of Tianjin Nankai Hospital. Qualified subjects will be assigned randomly either to the APP group or to the APP sham stimulation group on the basis of random numbers generated using SPSS 19.0. A specifically appointed investigator will be responsible for the randomization. The APP therapy (or sham stimulation) will be performed 6 h after surgery and every 12 h subsequently; six sessions will be conducted, each lasting 3 min. The first evaluation will be performed immediately before the first treatment (6 h after surgery) and, then, every 12 h for seven evaluations. The primary outcome is the time to first passage of flatus after surgery; the secondary outcome measures are abdominal distension, nausea, vomiting, time to first defecation, psychological status, and quality of life.

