## Background

Gastrointestinal dysfunction is a common complication of abdominal surgery; its main symptoms include delayed flatus and defecation, abdominal distention, abdominal pain, nausea, and vomiting. Therefore, promoting rapid recovery from gastrointestinal function has become integral to postoperative rehabilitation [1]. Gastric motility typically recovers within 24–48 h after surgery, whereas colonic motility is generally restored within 48–72 h [2]. Thus, it often takes 2–3 days for the patient to recover from gastrointestinal dysfunction. Postoperative gastrointestinal dysfunction is usually treated using alvimopan; however, this drug has adverse effects such as nausea and vomiting [3].

Auricular point acupressure (APP) may be a noninvasive physical treatment for the condition of postoperative gastronintestinal dysfunction [4, 5]. This therapy involves stimulating sensitive points on the auricle using vaccaria seeds; the points correspond to specific organs. In previous studies, we compared subjects’ postoperative time to flatus between an experimental group that received APP using vaccaria seeds on the large intestine point (CO7; 20.19 ± 3.14) and a control group that received APP sham stimulation (30.82 ± 5.58). Preliminary results showed that the APP using vaccaria seeds on CO7 can promote the recovery of gastrointestinal motility after abdominal surgery.

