### Randomization

Complete randomization will be performed using the random number generator in SPSS 19.0; patients will be randomly assigned to the APP therapy group or the APP sham stimulation group. To reduce selection bias and confounding factors, the randomization will be performed by a single specifically appointed investigator. Each group will contain an equal number of participants. When a qualified subject participates in the trial, the recruiters will obtain the subject’s sequence number from the assigning investigator; the two groups will be assigned to separate wards to prevent communication between them. Thus, bias will be reduced further.

To prevent researcher bias from confounding the results, the randomization will be blinded using the sealed envelope method: the subject recruiters and evaluators will not be informed of the allocation sequence, and the allocation sequence will be placed in sequentially numbered, opaque, sealed envelopes (to ensure that the contents cannot be seen, even under bright light). To prevent the allocation sequence from being disrupted, the subjects’ names and dates of birth will be written on the envelopes, the envelopes will be sealed, and detailed information regarding the subjects will be recorded in a video. The information will be copied onto assignment cards, which are contained in the envelopes, using carbon paper, and a second researcher will watch the video to confirm that the envelopes are still sealed after the subjects’ names are written. A video recorder will be used to record the complete process of opening the envelopes.

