### Intervention

After surgery, all the included subjects will lie in the supine position without a pillow and fast. The subjects will be given a liquid diet on the day after surgery. The APP therapy (or sham therapy) will be performed 6 h after the operation and every 12 h subsequently, for six treatment sessions, each lasting 3 min. The first evaluation will be performed 6 h after the operation, immediately before the first treatment. The patients will be then evaluated once every 12 h, for seven evaluations. The acupuncture points will be selected on the basis of the Nogier auricular point diagram [8]. Specifically, CO7 will be selected (the anterior 1/3 between the helix crus/part of the helix and the AB line, i.e., the auricular concha zone 7; Fig. 2). Operators will bring the required tools to the subject’s bedside and help the subject assume a comfortable position. The operator will then hold the upper posterior corner of the helix with one hand, and find the sensitive points with an auricular point detector (XS-100A; Guangzhou City Strong Medical Technology Co. Ltd., Guangzhou, China) using the other hand. The area will be disinfected using 75 % alcohol, and the vaccaria seeds will be attached to the auricular points.

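### The clock for first flatus and first defecation starts at return to the ward, not at surgery, and the two arms are on separate wards, so a ward-driven difference in return time would enter the treatment effect

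*Protocol article*

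**What the plan says.** The abstract (Methods/design) states: "The primary outcome is the time to first passage of flatus after surgery". The Background likewise describes the preliminary data as postoperative: "we compared subjects’ postoperative time to flatus between an experimental group".

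The only operational definition is under Outcome measures. There the start of the clock is given as "we will begin observing and recording when subjects return safely to the ward", patients and families note the time of first flatus, and "The interval between the two time points will be then calculated". Time to first defecation is built in the same way.

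Treatment runs on a different clock. Under Intervention, "The APP therapy (or sham therapy) will be performed 6 h after the operation and every 12 h subsequently". Pain, distension, nausea and vomiting are also first assessed 6 h after surgery and then every 12 h.

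Under Randomization, "the two groups will be assigned to separate wards to prevent communication between them". Under Statistical analysis, for the primary outcome, "the experimental and control groups will be statistically compared using two independent-sample *t* tests". No covariate is named, and the surgery-to-ward interval is not among the listed baseline or clinical data.

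**The concern.** A delay between surgery and the start of the clock is usually harmless in a randomised trial. It adds a little variance and averages out between arms. This design gives less assurance, because the starting event takes place on a different ward for each arm. If one ward receives patients later, or logs arrival by a different habit, all of its patients have a shorter recorded time to flatus for the same true recovery, and all of them are in one arm. The definition also depends on a patient having returned safely, which the text does not define, so ward staff have some latitude over when the clock starts.

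At stake is the primary comparison. The target difference is 4 h, so a ward difference of a fraction of an hour to an hour would be a visible share of it. It could mimic benefit or hide it. First defecation carries the same exposure.

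**Working it through.** **Reproducing the plan's sample size.** Inputs from Sample size estimation: SDs 3.14 and 5.58 h, difference 4 h, z values 1.96 and 0.84, dropout 15%.

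- Sum of variances: 3.14² + 5.58² = 9.8596 + 31.1364 = 40.996.
- n = (1.96 + 0.84)² × 40.996 / 4² = 7.84 × 40.996 / 16 = 20.09 per group, rounded up to 21.
- 21 / 0.85 = 24.7, so 25 per group and 50 in total.

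This agrees with the plan. The sample size is not in error.

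**How a ward difference enters the estimate.** For each patient, recorded time = (surgery to flatus) − (surgery to ward return). Taking arm means and subtracting:

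estimated difference = true difference from surgery − difference between arms in mean surgery-to-ward interval.

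If the two wards have the same mean interval, the second term is zero in expectation. If they differ by d hours, the estimate shifts by exactly d, with sign set by which ward is later.

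**Illustrative size.** The documents give no value for d, so the values below are assumptions. With 21 evaluable per arm:

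- SE = √(40.996 / 21) = 1.397 h.
- False-positive rate with no true effect: Φ(d/SE − 1.96) + Φ(−d/SE − 1.96).
- Power for a true 4 h when the shift works against treatment: Φ((4 − d)/SE − 1.96).

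Worked example, d = 1 h: d/SE = 0.716, so the false-positive rate is Φ(−1.244) + Φ(−2.676) = 11.0%. For power, (4 − 1)/SE = 2.147 and Φ(0.187) = 57.4%.

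| Assumed d | Share of 4 h | False positives, normal approx. | False positives, simulated Welch t | Power, normal approx. | Power, simulated Welch t |
|---|---|---|---|---|---|
| 0 | 0% | 5.0% | 5.0% | 81.7% | 79% |
| 0.25 h | 6.25% | 5.4% | 5.3% | 76.5% | not quoted |
| 0.5 h | 12.5% | 6.5% | about 6.4% | 70.7% | 68% |
| 1 h | 25% | 11.0% | about 10.6% | 57.4% | 55% |
| 2 h | 50% | 29.9% | 28% | 29.9% | 28% |

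The simulated columns use Welch tests on normal data with the plan's SDs. They fall slightly below the normal approximation because t critical values are larger. If the shift favours treatment, normal-approximation power rises instead, to 89.6% at 0.5 h and 94.7% at 1 h.

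**The case against.** The strongest case against is that nothing in the documents shows a ward difference. Patients come from one department of one hospital, are ASA I–II, and have laparoscopic cholecystectomy alone. A recovery-room delay common to both arms cancels, and at 0.5 h the false-positive rate moves only from 5% to about 6.4%. This stands, and it limits the point to a conditional one.

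Four stronger readings are tempting, and the documents do not support them.

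- **That the protocol has two competing definitions of the endpoint.** Only the Outcome measures section says how the interval is calculated. The abstract may be loose shorthand, and the Intervention section times treatment, not the endpoint. The mismatch should be removed, but an analyst would follow the outcome definition.
- **That randomisation cannot balance the delay.** The moment of allocation is not stated. Enrolment of patients scheduled for surgery and assessments 24 h before it suggest that patients enter before surgery, but enrolment is not allocation, and treatment starts only at 6 h. If allocation followed ward return, time zero would precede it and be balanced in expectation. Even if allocation came first, randomisation balances the patient-driven part of the delay. Only a ward-driven part could bias.
- **That the bias could never be detected.** The 6 h schedule requires staff to know when surgery ended, and ward return is recorded as the start of the clock. The delay could therefore be compared by arm. No such comparison is written into the plan.
- **That correcting the origin cures the separate-ward problem.** It closes this one route. Differences between wards in care or in outcome recording remain confounded with arm whatever the origin.

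**Conclusion.** The point holds in conditional form. The primary outcome and first defecation are timed from an event that occurs on an arm-specific ward, while the abstract and the treatment schedule refer to surgery. Any ward-driven difference in return time or in recording arrival would shift the effect hour for hour, and the planned test makes no allowance for it. This requires that such a difference exists and that allocation comes before ward return; neither is documented. The percentages above illustrate sensitivity to assumed shifts of 0.25 to 2 h and do not estimate actual bias. The correction is worth making because it is cheap and removes an avoidable dependence of the primary endpoint on the ward.

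**What to change.** - Define time zero for both first flatus and first defecation as the end of surgery, taken from the operation or anaesthesia record in the same way in both arms.
- Word the abstract and the Outcome measures section so that they name this same origin.
- Keep ward-arrival time as a separate recorded variable, and report the surgery-to-ward interval by arm so that readers can see whether the wards differed.

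**Cost.** One sentence and one extra time on the case report form, with no added procedure. The preliminary SDs (3.14 and 5.58 h) and the 4 h target must be confirmed to apply to the end-of-surgery origin. If they do, the planned 50 patients stand; if they were measured from ward return, the calculation should be rerun. The change does not address other differences between the wards, which need separate consideration.
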